#### Eligibility criteria for clusters (health centers) and participants

The trial will take place in specific primary health centres that meet the eligibility criteria outlined in the pre-formative phase objectives. A woman can participate in the study if

She comes to the family planning clinic with the intention to (a) use contraception for the first time in her life (new user) or (b) switch from a contraceptive method to another one (switching user) or (c) resume a method after not using any in the prior 3 months (lapse user), or (d) discontinue a modern method (discontinuing user).She is not coming for the resupply of a currently used method, such as pills or injectables.She has the intention to continue her follow-up at the health centre during the 12-month study follow-up.She does not participate in another study.She provides informed consent.

Exclusion criteria: not willing to participate in the complete duration of the trial.

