**Methods:**

A multisite, two-stage and five-phase intervention design will start with a pre-formative, formative, design, experimental and reflective phase. The pre-formative phase will map potential study sites and establish the sampling frame. The two-part formative phase will first use participatory approaches to identify clients’ perspectives, including young couples and providers, to ensure research contextualisation and address each interest group’s needs and priorities followed by clinical observations of client–provider encounters to document routine care. The design workshop in the third phase will result in the development of a package of contraceptive counselling interventions. In the fourth experimental phase, a multi-intervention, three-arm, single-blinded, parallel cluster randomised-controlled trial will compare routine care (arm 1) with the contraceptive counselling package (arm 2) and the same package combined with wider methods availability (arm 3). The study aims to enrol a total of 7920 participants. The reflective phase aims to identify implementation barriers and enablers. The outcomes are clients’ level of decision-making autonomy and use of modern contraceptives.

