Building on this systematic review, the WHO organised a geographically diverse think tank in May 2019 in Geneva, Switzerland, to identify research and guidance gaps and other opportunities to improve the quality of contraceptive counselling.^32^ Equally important was the crafting of a definition on contraceptive counselling, which was adopted by think tank members^33^ : *Contraceptive counselling is defined as the exchange of information on contraceptive methods based on an assessment of the client’s needs, preferences and lifestyle to support decision-making as per the client’s intentions. This includes the selection, discontinuation or switching of a contraceptive method. The key principles are based on coercion-free and informed choice; neutral, understandable and evidence-based information; collaborative and confidential decision-making process; ensuring respectful care, dignity and choice*. The definition took into consideration the core dimensions articulated in the literature and mirrors the principles that were deliberated by the think tank: a two-way discussion and decision-making process between the client and provider, sharing objective and user-friendly information, and fundamentally grounded in the rights to autonomy, dignity, privacy, respect and participation, among others. In addition, person-centeredness is a critical component of quality in family planning.^5^ The four-item person-centred contraceptive counselling scale (PCCC) is a valid and reliable measure of person-centred contraceptive counselling that reflects patients’ perspectives on contraceptive counselling.^34^ For example, integrating Dehlendorf’s four-item validated tool: PCCC: person-centred contraceptive counselling scale: Think about your visit. How do you think the member of the healthcare team did? Please rate them on each of the following by circling a number (the scale will use—Poor, Fair, Good, Very good and Excellent). Hence, to measure decision-making autonomy, the following considerations need to factor:

Respecting me as a person.Letting me say what mattered to me about my birth control method.Taking my preferences about birth control seriously.Giving me enough information to make the best decision about my birth control method.

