### Study overall objective and hypothesis

Owing to these gaps combined with the sociocultural challenges related to accessing contraception, we propose a multisite, two-stage and five-phase study with two main objectives. The objective is to identify and test the effectiveness of a contraceptive counselling intervention bundle on improving clients’ informed decision-making autonomy as well as meeting their need for family planning. The outcomes are changes in clients’ decision-making autonomy and clients’ met need for family planning. The secondary outcome will be a change in modern contraceptive prevalence.

The research rests on the working hypotheses that the package will strengthen existing contraceptive counselling services; incorporate perspectives of key stakeholders such as clients and providers; align with national health policies and WHO global standards and address challenges related to limited public resources.

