#### Outcome measures

Quantitative indicators will be captured in case-report forms (CRFs) developed and piloted at the country level before finalisation. The proposed outcomes to be assessed after each visit, at mid-point (6 months after enrollment) and at the study end (12 months after enrollment) are oriented toward clients and consist of levels of clients’ decision-making autonomy and demand satisfied for family planning.

To determine their level of decision-making autonomy, clients will be asked to answer questions about the different domains contained in the counselling definition (see the Background section). These domains comprise client–provider collaboration, client’s needs and preferences, the quality of information, freedom from coercion, confidentiality and dignity. The PCCC, developed and tested in publicly funded clinics in California, will also be used.^43^ The four PCCC questions fall under the domains of respect, eliciting—and giving serious consideration to—client’s preferences, and information quality and it will be assessed during the intervention phase as per described by UNFPA to measure decision-making autonomy SDG 5.6.1.^44^

The study proposes nonetheless the another outcome, while acknowledging its limitations: modern contraceptive prevalence after the first visit and at 6 and 12 months after enrollment.

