#### Statistical analysis

We will prepare a comprehensive statistical analysis plan. Participants will form the unit of analysis and the clustered nature of the data will be accounted for. All analyses will be by intention to treat. For continuous variables, we will compute means, SD, minimum and maximum values, and for categorical variables, we will compute frequencies and percentages. We will look at the distribution of variables and see if there are any outliers as part of data quality control and descriptive analysis. Descriptive statistics will be tabulated for individual clusters and aggregated across clusters. Within each of the three groups/arms of the study (two experimental and one control), outcome differences between final (12 months after enrolment) and intermediate (6 months after enrolment) outcome measurements will be obtained, and these changes will be compared between the control group and each of the two experimental groups. For categorical outcomes, χ^2^ tests for two independent proportions will be used, and for continuous variables, Student’s t-tests for two independent means will be used. We will use IBM SPSS Statistics 25, R V.3.6.2, STATA V.16.1 or SAS V.9.4 statistical packages for the analysis. The findings will be presented using the CONSORT Statement checklist from 2010 and its extension for cluster studies.^45^

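### Modern contraceptive prevalence pools women who came to stop a modern method with women who came to start, resume or switch, and the named tests do not use this user type

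*Protocol article*

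**What the plan says.** All references are to the protocol article.

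- **Eligibility criteria for clusters and participants.** Four user types may enrol: (a) new users, (b) switching users, (c) lapse users with no method in the prior 3 months, and (d) women who come to "discontinue a modern method (discontinuing user". Women coming only for resupply are not eligible.
- **Background, definition of counselling.** Counselling supports decisions that follow the client's own intentions: "This includes the selection, discontinuation or switching of a contraceptive method".
- **Outcome measures.** A further outcome is "modern contraceptive prevalence after the first visit and at 6 and 12 months after enrollment". It is introduced "while acknowledging its limitations", but the limitations are not named, and no distinction by user type is made.
- **Rank of that outcome.** Study overall objective and hypothesis: "The secondary outcome will be a change in modern contraceptive prevalence". The Methods paragraph of the abstract lists the outcomes as "decision-making autonomy and use of modern contraceptives", without ranking them.
- **Statistical analysis.** "All analyses will be by intention to treat". For the comparison between control and each experimental arm, "outcome differences between final (12 months after enrolment) and intermediate (6 months after enrolment) outcome measurements will be obtained" within each arm and then compared. Chi-square and Student's t-tests are named. The section also says that clustering will be accounted for and that a full statistical analysis plan will be prepared.
- **Cluster RCT and Randomisation.** Centres are matched on facility-level and district-level variables; user type is not among them. Centres are randomised first and then recruit consecutively. Participants and providers are not blinded.

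**The concern.** For a woman in group (d), counselling that meets the article's own definition may end with her using no modern method. She can then score well on decision-making autonomy and be a non-user in the prevalence figure. Within this group the two outcomes can move in opposite directions for the same good encounter. A pooled prevalence figure cannot show whether a small or absent difference means that the package did little or that it respected more wishes to stop.

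User type also fixes much of a woman's starting status. New and lapse users enter on no method, discontinuing users enter on a modern one, and switching users enter on some method. It is thus a plausible baseline predictor of modern use, though the article gives no figure for its strength. Because women are recruited unblinded after their centre has been allocated, the mix of user types could differ between arms.

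**Working it through.** **What can be reproduced.** The article gives no significance level, power, effect size, baseline rate, intracluster correlation (ICC) or dropout, so the sample size cannot be re-derived. Taking 7920 as the total for both countries, with 36 centres in each: 7920/72 = 110 women per centre, 24 centres per arm, and 24 × 110 = 2640 women per arm.

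**Step 1: effect on the prevalence level.** Let *s* be the share of discontinuing users, D₁ the arm difference in modern use among groups (a) to (c), and D₂ the difference in group (d). Then

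pooled difference = (1 − s) × D₁ + s × D₂.

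The contribution of group (d) alone is s × D₂. With D₂ = −20 points (assumed):

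- s = 5%: 0.05 × 20 = 1 point lower
- s = 15%: 0.15 × 20 = 3 points lower

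If counselling instead kept 20 points more of group (d) on a modern method, the same sum gives 1 to 3 points higher. The pooled figure is hard to read in either direction.

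**Step 2: effect on a true gain elsewhere.** Assume modern use of 70% against 75% in groups (a) to (c), so D₁ = +5 points, and 40% in control for group (d).

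| s | D₂ = 0 (40% vs 40%) | D₂ = −20 (40% vs 20%) |
|---|---|---|
| 5% | +4.75 | +3.75 |
| 10% | +4.5 | +2.5 |
| 20% | +4.0 | 0.0 |
| 30% | +3.5 | −2.5 |

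The gain is cancelled at s = 5/(5 + g), where g is the fall in group (d): 33%, 20% or 14% for a fall of 10, 20 or 30 points.

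**Step 3: the stated contrast.** Score use as 1 and non-use as 0. A woman who stops at the first visit and stays off scores 0 at 6 months and 0 at 12 months, so her change is 0. She is not a failure in this contrast. She reduces the change seen in the other women by the factor (1 − s), which is 0.95 at s = 5% and 0.85 at s = 15%.

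**Step 4: scale.** Assume prevalence 50%, two-sided 5% level and 80% power (multiplier 2.8). The detectable difference in levels is 2.8 × √(2 × 0.25/2640 × DE), with DE = 1 + 109 × ICC and no allowance for matching or dropout:

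- ICC 0.01: DE = 2.09, 5.6 points
- ICC 0.05: DE = 6.45, 9.8 points

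**Step 5: chance imbalance in user mix.** The 95% half-width for the difference in *s* between two arms is 1.96 × √(2 × s(1 − s) × DE/2640). It is 1.6 points (ICC 0) to 5.6 points (ICC 0.10) at s = 10%, and 2.2 to 7.4 points at s = 20%. If modern use differs by 50 points between user types (assumed), this moves the comparison of levels by about 0.8 to 3.7 points. Adjustment matters most when user mix varies between centres.

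**The case against.** The strongest reply is that this touches a secondary outcome which the article already introduces with a caveat. The main outcomes are autonomy and met need or demand satisfied; autonomy does not penalise a decision to stop. The shift of 1 to 3 points is assumed and lies below the 5.6 to 9.8 points that the trial could detect. Its direction is assumed too: the Background reports that structured counselling on side-effects tends to favour continuation, so some women in group (d) may freely continue or switch. All of this stands, and it limits the weight of the point.

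A reader might infer four stronger things, none of which the article supports:

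- **That an honoured stop counts as failure in the planned comparison.** The only between-arm contrast described is the change from 6 to 12 months, where an immediate and lasting stop contributes zero. The penalty applies to the levels, which the Outcome measures section lists.
- **That user type is left out of the analysis.** The named tests do not use it, but covariates and strata are commonly set in the statistical analysis plan, which is announced and not shown.
- **That the expanded method range draws more switching users.** Nothing in the article shows this. A difference in mix is possible, not established.
- **That group (d) should be removed from prevalence, or demand satisfied redefined.** Removal could hide continuation or switching by free choice. No error in demand satisfied is shown, and its denominator is not spelled out in the article.

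**Conclusion.** The point holds in a limited form. The eligibility criteria, the counselling definition and the undifferentiated prevalence outcome do not fit together for women who come to stop. In the levels after the first visit and at 6 and 12 months, a respected choice is counted as non-use; in the 12-minus-6-month contrast the effect is mainly dilution.

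The size is about 1 to 3 points on the prevalence level if 5 to 15% of women are discontinuing users and 20 points more of them stop. Complete cancellation of a 5-point gain would need a 20% share together with that 20-point fall. The share, the rates and the ICCs are all assumptions. This is a problem of interpreting a secondary outcome and does not undermine the trial's main conclusions. It is still worth correcting, because user type is known before counselling, recruitment is unblinded after allocation, and the remedy is nearly free.

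**What to change.** 1. Keep all women in the intention-to-treat analysis.
2. Record user type at eligibility, before counselling, and present modern contraceptive prevalence by it at every time point: groups (a) to (c) against group (d). State that an intended discontinuation in group (d) is not read as failure.
3. Replace the plain chi-square and t-tests with between-arm models that account for clustering and adjust for user type. Report the user mix by arm, so that any difference arising at recruitment is visible.
4. Leave autonomy and the demand-satisfied denominator unchanged.

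If the statistical analysis plan already does this, a sentence in the article's outcome and analysis sections is enough. The cost is wording and one extra table: eligibility already requires user type to be established, no woman is dropped, and the sample size does not change. The estimate within group (d) may be imprecise if that group is small.

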#### Interventions

The primary health centres assigned to the first experimental group will implement the intervention package. Meanwhile, those in the second experimental group will implement the intervention package along with an expanded range of family planning methods recommended by national guidelines. The control group will continue with usual care practices.

Depending on the specific components of the intervention package, certain interventions, such as provider capacity building, may be implemented prior to participant recruitment to ensure readiness and effectiveness of the interventions during the study period.

#### Randomisation

In each country, a total of 36 sites will be selected and matched into 12 trios based on the specified criteria. Within each trio, the study sites will be randomly assigned to one of three study arms at a 1:1:1 ratio. This randomisation process will be repeated 12 times, once for each trio. The randomisation process will not have any restrictions, and blinding (masking) of participants and providers cannot be implemented except for data analysts who will handle the study data independently. The study clusters will include all consecutive and eligible participants until the total sample size of 7920 participants is reached.

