### Cluster RCT

The research will be a multi-intervention, three-arm, single-blinded, parallel, cluster RCT done in selected primary health centres (clusters) in Pakistan and in Nigeria (see figure 2 for the cluster RCT flow diagram, and figure 3 for the schedule of enrolment, interventions and assessments (Standard Protocol Items: Recommendations for Interventional Trials template). Centres will be randomly allocated to the three study arms in matched ratios (1:1:1) on the basis of the number of monthly family planning encounters, the number of available contraceptive types, the ratio of health workers per population in the clinic coverage zone, the location in urban or rural settings and selected district-level variables that may have an influence on the study outcomes, including the unmet need for family planning, the level of literacy among women and household income terciles. Only data analysts will be masked/blinded to trial-arm allocation. Service providers skilled in family planning services will implement the clinical components of the contraceptive counselling package.

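### Centres are randomised within matched trios, but the named between-arm tests are for independent samples and carry no trio term, so any precision gained by matching is lost

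*Protocol article*

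**What the plan says.** Design. The Randomisation section states: "In each country, a total of 36 sites will be selected and matched into 12 trios based on the specified criteria". It continues: "Within each trio, the study sites will be randomly assigned to one of three study arms at a 1:1:1 ratio". The Cluster RCT section gives the basis of matching, with allocation "in matched ratios (1:1:1) on the basis of the number of monthly family planning encounters", followed by the number of contraceptive types, the staffing ratio, urban or rural location, and district variables chosen because they may affect the outcomes. The Randomisation section then adds: "The randomisation process will not have any restrictions".

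Analysis. The Statistical analysis section promises a full analysis plan and says: "Participants will form the unit of analysis and the clustered nature of the data will be accounted for". It compares changes between the 6-month and 12-month measurements, control against each experimental arm. For categorical outcomes it names chi-square tests for two independent proportions. For continuous outcomes it says that Student's "t-tests for two independent means will be used". Trio, matched set, stratum and country do not appear in that section.

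**The concern.** Three centres in a trio are chosen because they resemble one another on factors expected to predict the outcome, and each goes to a different arm. The arms are therefore not independent samples of centres. If the matching factors do predict the outcome, the centre means within a trio are positively correlated, and the variance of an arm difference is smaller than an independent-samples formula assumes. A test without trio then uses too large a standard error: its intervals are wider than the design warrants, and power is given up after the matching has been done.

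Accounting for centre does not solve this. A random effect for centre, or an analysis of centre means, deals with correlation among women at the same centre. It leaves the correlation between centres of the same trio unmodelled.

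The sentence on restrictions adds to the problem. Allocation within trios is itself a restriction, so the wording, read alone, describes a different design from the sentences before it.

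**Working it through.** **What can be reproduced.** Two countries × 36 centres = 72 centres in 24 trios, and 7920 / 72 = 110 women per centre, or 7920 / 3 = 2640 per arm. The article gives no alpha, power, effect size, ICC or matching correlation, so 7920 cannot be traced to a power calculation. Everything below rests on assumed values.

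**Assumptions (not in the document).** Two-sided alpha 0.05; 110 per centre; 24 trios; binary outcome level near 50% (variance 0.25); 8-point difference; ICC 0.02 or 0.05; share *s* of between-centre variance explained by trio of 0, 0.3 or 0.5.

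**Formulas.** Variance of a centre mean, in units of the outcome variance:

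- ignoring trio: v0 = ICC + (1 − ICC)/110
- within trio: v1 = ICC(1 − s) + (1 − ICC)/110
- SE of an arm difference = √(0.25 × 2 × v / 24)

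**Standard errors.**

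| ICC | s | v0 | v1 | SE ignoring trio | SE using trio | Ratio |
|---|---|---|---|---|---|---|
| 0.02 | 0.3 | 0.0289 | 0.0229 | 0.0245 | 0.0218 | 0.89 |
| 0.02 | 0.5 | 0.0289 | 0.0189 | 0.0245 | 0.0198 | 0.81 |
| 0.05 | 0.3 | 0.0586 | 0.0436 | 0.0350 | 0.0302 | 0.86 |
| 0.05 | 0.5 | 0.0586 | 0.0336 | 0.0350 | 0.0265 | 0.76 |

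**Power must be compared at the same *s*.** When matching works, the true variance of the difference falls whichever test is used, so the test that ignores trio gains a little as well. I simulated t-tests on centre means, independent-samples against paired within trio:

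| ICC | s | Power, ignoring trio | Power, using trio | Type I error, ignoring trio |
|---|---|---|---|---|
| 0.05 | 0 | 61% | 59% | 0.05 |
| 0.05 | 0.3 | 63% | 72% | about 0.025 |
| 0.05 | 0.5 | 64% | 82% | about 0.012 |
| 0.02 | 0.3 | 92% | 94% | 0.03 |
| 0.02 | 0.5 | 93% | 97% | 0.02 |

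The test using trio keeps its type I error at about 0.05 throughout. A normal approximation at ICC 0.05 gives 65% against 76% (s = 0.3) and 67% against 86% (s = 0.5); the t-test figures are preferable with 24 trios.

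**Degrees of freedom.** In a three-arm model of centre means, adding trio takes the residual from 72 − 3 = 69 to 72 − 24 − 2 = 46 pooled, and from 36 − 3 = 33 to 36 − 12 − 2 = 22 per country. Pairwise within-trio differences leave 24 − 1 = 23 pooled or 12 − 1 = 11 per country.

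**The case against.** **The analysis plan may settle it.** A condensed article may leave model terms to its analysis plan, and this one promises such a plan and says that clustering will be handled. That would answer a complaint about silence. But the article is not silent: it names tests for independent samples, which do not fit allocation within trios, and a plan that followed it would carry the mismatch forward.

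**The named tests, read literally, do the opposite harm.** A reader might infer that this point is about false positives. Run on individual women with no adjustment, the named t-test would indeed inflate type I error: in a simulation with 24 trios of 110 per centre at ICC 0.05, to 0.22–0.44 as *s* goes from 0.7 down to 0. That comes from ignoring centre, which the same section says will not happen. Once centre is handled, leaving out trio neither biases the comparison nor inflates type I error. What remains is a loss of efficiency.

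**The size is uncertain.** This stands. ICC, *s* and the effect size come from outside the document. The figures also model an outcome level, whereas the protocol compares changes from 6 to 12 months. The matching factors are largely stable traits of centre or district, and a change score tends to remove those, so the gain for the stated contrast could be smaller. Country differences enter the error term only if the countries are pooled, which the article does not say.

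**The sentence on restrictions may mean no further restriction.** That is a natural reading after the description of the trios. It makes this a wording fix, but one worth making.

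**Conclusion.** The point holds as a mismatch between the stated randomisation and the stated tests. With clustering handled and trio omitted, the analysis is valid but conservative when matching is effective. Under the assumptions listed, the loss is about 9 to 18 power points at ICC 0.05 and about 2 to 4 at ICC 0.02. If trio explains nothing, there is no loss, and using trio costs about 2 points at ICC 0.05.

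A reader might set 63%, the normal-approximation power when matching explains nothing, against 86%, the power when it explains half, and conclude that over 20 points are at stake. That compares two different states of the world, and the document supports neither value of the matching correlation. Nor does it support saying that the trial's result would be biased. The change is worth making because it aligns the analysis with the randomisation at little cost, not because the size of the loss is known.

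**What to change.** Replace the independent-sample tests in the Statistical analysis section with an analysis that carries both centre and trio. Two options fit: a mixed model with a random effect for centre and trio as stratum, with a small-sample correction, or an analysis of within-trio differences between centre-level summaries. In a pooled analysis, trio also absorbs country, because trios are formed within country.

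In the Randomisation section, replace the sentence on restrictions with one saying that allocation is stratified by matched trio with no further restriction.

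The cost is one model term, one corrected sentence and fewer degrees of freedom: 46 pooled or 22 per country in the three-arm model, and 23 or 11 for pairwise within-trio differences. The last is the tightest, with a critical t of 2.20. If the countries are to be analysed separately, the three-arm model is therefore the better choice.

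### Women are recruited after their centre's arm is set, without masking on site, and the named tests adjust for no client characteristic, so differences in user mix can enter the arm comparison

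*Protocol article*

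**What the plan says.** All references are to the protocol article.

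- **Allocation.** Under Randomisation, "In each country, a total of 36 sites will be selected and matched into 12 trios", and within each trio "the study sites will be randomly assigned to one of three study arms at a 1:1:1 ratio". The unit allocated is the centre. The Cluster RCT section lists the matching variables, which describe centres and districts.
- **Timing.** Under Interventions, and depending on what the package contains, "certain interventions, such as provider capacity building, may be implemented prior to participant recruitment".
- **Masking.** Under Randomisation, "blinding (masking) of participants and providers cannot be implemented except for data analysts". The Cluster RCT section likewise limits masking to the analysts.
- **Entry.** The participant criteria begin "She comes to the family planning clinic with the intention to" and then list four user types: new, switching, lapsed and discontinuing. Women attending for resupply are not eligible. A woman must also intend to stay in follow-up for 12 months and must consent.
- **Safeguard.** "The study clusters will include all consecutive and eligible participants until the total sample size of 7920 participants is reached".
- **Outcomes.** Outcome measures places autonomy and demand satisfied after each visit and at 6 and 12 months, and modern contraceptive use after the first visit and at the same two later times.
- **Analysis.** Statistical analysis compares the change between 6 and 12 months between control and each experimental arm. Chi-square tests serve categorical outcomes, and for continuous ones "Student’s t-tests for two independent means will be used". Clustering is to be taken into account by a method not given, and a full analysis plan is announced.

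**The concern.** In a trial that randomises centres and then recruits people, randomisation protects the comparison of centres. It does not by itself protect the comparison of the people who later enrol. If the arm affects who comes, who is judged eligible or who agrees to take part, the arms can differ at entry for reasons unrelated to any effect on an individual woman.

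The conditions for this are present. The arm is fixed before women are screened, providers may already be trained, and nobody on site is described as masked. Several entry criteria rest on what a woman says she intends. The sample also mixes women who come to start a method with women who come to stop one, while modern use is itself an outcome. Even a modest difference between arms in that mix could look like an effect on use, met need or autonomy.

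**Working it through.** **Layout.** The article gives no alpha, power, effect size or intracluster correlation (ICC), so 7920 cannot be rebuilt from a power formula. The layout is consistent: 2 countries × 36 centres = 72 centres, and 7920 / 72 = 110 women per centre. Each arm has 7920 / 3 = 2640 women in 24 centres. This takes 7920 as the total over both countries, recruited evenly.

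**Inputs for the illustration.** The documents give no outcome rates by user type and no expected mix by arm. All of these are assumptions:

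- difference between arms in the share of one user type (shift): 10 points
- difference in outcome between user types (gap): 20 to 40 points

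**Level outcomes.** Bias = shift × gap.

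- 0.10 × 20 = 2 points
- 0.10 × 40 = 4 points
- A milder case, a 2-point shift with a 20-point gap: 0.02 × 20 = 0.4 points

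**6-to-12-month change.** Bias = shift × (gap at 12 months − gap at 6 months). With a 10-point shift:

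| Gap at 6 months | Gap at 12 months | Bias in 12-month level | Bias in the change |
|---|---|---|---|
| 40 | 40 | 4 | 0 |
| 40 | 30 | 3 | −1 |
| 40 | 20 | 2 | −2 |

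A stable difference in mix cancels in the change. What remains depends on how far the user types converge or diverge between the two times.

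**Does accounting for clustering help?** For a level outcome, take a proportion of 0.5, n = 2640 per arm and a design effect of 1 + 109 × ICC. Then SE = √(2 × 0.5 × 0.5 / 2640 × design effect). With bias b and no true effect, the chance of p < 0.05 is Φ(b/SE − 1.96) + Φ(−b/SE − 1.96).

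| Bias | Clustering ignored | ICC 0.01 | ICC 0.02 | ICC 0.05 |
|---|---|---|---|---|
| 0.4 points | 6% | 5.5% | 5.3% | 5.2% |
| 2 points | 31% | 17% | 13% | 9% |
| 4 points | 83% | 52% | 37% | 21% |

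Allowing for clustering widens the interval and so lowers these chances. It leaves the bias itself unchanged.

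**The case against.** Four points on the other side carry weight.

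1. **The comparison is of change, not level.** A reader might infer that recruitment differences pass straight into the trial's comparison. The article does not support that. The contrast it fixes is the 6-to-12-month change, in which a constant gap between user types drops out. The full bias applies only to levels, which are outcomes too: modern use after the first visit and autonomy after each visit.
2. **The entry text leaves less room than it might.** Intention is tied to the woman's purpose in coming to the clinic. New and lapsed use rest partly on history, and enrolment is consecutive. This restricts selection by staff. It leaves open consent, the stated intention to stay, the judgement of intention, and any difference in who attends.
3. **The tests are not declared blind to everything.** A reader might conclude that the analysis ignores clustering or that no covariate adjustment is planned. The article says that clustering will be handled, and the announced analysis plan may contain covariates. What stands is narrower: the tests that the article does name adjust for no client characteristic.
4. **The recruiter is not identified.** That screening is done by unmasked staff is an inference. The article never says who screens and takes consent in the trial, only that nobody apart from analysts is masked. The screening procedure may also sit in the study manual.

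Two further limits apply. Intervention before recruitment is stated as a possibility, for a package not yet developed. That the wider method range in the third arm would attract more switching users is plausible, but nothing in the article shows it.

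**Conclusion.** The concern holds as a risk with a cheap remedy, not as a demonstrated bias. Recruitment follows allocation without masking on site, entry rests partly on stated intention and consent, and the only recruitment safeguard stated is consecutive enrolment. Matching of centres cannot balance women who enrol later, and the named tests would not correct an imbalance in user mix.

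The illustrated size is 2 to 4 points on a level outcome. On the 6-to-12-month change it is 0 with a constant gap, and 1 to 2 points in size if a 40-point gap narrows to 30 or 20. These figures rest wholly on the assumed 10-point shift and 20 to 40-point gap; a 2-point shift with a 20-point gap gives only 0.4 points. They suit an outcome such as modern use. The documents give nothing from which to size the effect on autonomy or met need.

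**What to change.** 1. **Recruitment.** State that the research assistant already assigned to each centre (Data source and collection) establishes eligibility, records user type and takes consent on arrival, before any contact with the provider. Use the same arm-neutral script in all 72 centres.
2. **Analysis.** Replace the plain chi-square and t-tests with a cluster-adjusted regression. Pre-specify user type, age and current method as covariates, all recorded before counselling. The timing matters: a user type recorded after counselling may already reflect the intervention, and no later analysis plan can recover the earlier value.

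The cost is wording in the study manual and case-report form, a few minutes per attender, and a primary estimate that is adjusted rather than crude. The two steps reduce the bias but do not remove it, because unmeasured differences in who attends or consents remain.
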